### Sample size and power considerations

We estimate that a minimum total sample size of 120, with 60 in each arm, would provide power of 0.80 to detect a mean difference of 5 points in the PHQ-9 [44], assuming a repeated measures correlation of 0.6, and 2-tailed alpha of 0.05. This sample size also provides more than 80% power (two sided alpha = 0.05) to detect any between-group absolute difference in proportions of 15% or more (e.g., 45% of usual care patients achieve depression remission vs 60% of intervention patients) [29]. Anticipating a 40% attrition rate, we planned to recruit 168 patients in total across our 4 PCN sites. Although the model is implemented in 4 PCN sites, the individual general physicians affiliated with the PCN will carry out the changes in care. While we will include PCN site as a covariate in our analysis, because there are approximately 140 general physicians across these 4 PCN sites, we choose not to further inflate our sample to account for clustering of patients and their outcomes.

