**Methods/design:**

We initiated the TeamCare model in four Primary Care Networks in Northern Alberta. The intervention involves a nurse care manager guiding patient-centered care with family physicians and consultant physician specialists to monitor progress and develop tailored care plans. Patients eligible for the intervention will be identified using the Patient Health Questionnaire-9 as a screen for depressive symptoms. Care managers will then guide patients through three phases: 1) improving depressive symptoms, 2) improving blood glucose, blood pressure and cholesterol, and 3) improving lifestyle behaviors. We will employ the RE-AIM framework for a comprehensive and mixed-methods approach to our evaluation. Effectiveness will be assessed using a controlled “on-off” trial design, whereby eligible patients would be alternately enrolled in the TeamCare intervention or usual care on a monthly basis. All patients will be assessed at baseline, 6 and 12 months. Our primary analyses will be based on changes in two outcomes: depressive symptoms, and a multivariable, scaled marginal model for the combined outcome of global disease control (i.e., A1c, systolic blood pressure, LDL cholesterol). Our planned enrolment of 168 patients will provide greater than 80% power to observe clinically important improvements in all measured outcomes. Direct costing of all intervention components and measurement of all health care utilization using linked administrative databases will be used to determine the cost-effectiveness of the intervention relative to usual care.

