### Data analysis

As the initial focus of the intervention is on the management of depressive symptoms, we have considered the PHQ-9 as a main primary outcome, and will assess changes in PHQ-9 scores over 12-months between groups, adjusting for baseline PHQ-9 score, using a mixed effects multivariate model. For our second primary outcome of improvements in global disease control, we will employ a multivariate model that jointly tests the changes in multiple clinical outcomes, namely A1c, LDL cholesterol and systolic blood pressure [29]. Using the same analytic approach as in the recently published RCT of this intervention, we will apply a scaled marginal model [29,75] to simultaneously compare the change in these continuous outcomes at 12 months, adjusting for the baseline status for each variable. This approach scales the changes in each outcome by its standard errors, and thus the coefficients can be directly interpreted as effect sizes [29]. In either primary outcome analyses, the models will be estimated iteratively and the potential correlations among and between outcomes within individuals will be handled using generalized-estimating equation (GEE) models for each outcome [75].

We will also compare the study arms based on the proportion of subjects who achieved a remission of depression (i.e., PHQ-9 < 10 for 3 consecutive months) and the proportion of patients who achieve a clinically important change in the outcomes (that is, achieving a reduction of 5 points on the PHQ-9 [44] or a 10% or greater improvement over baseline values for A1C, LDL cholesterol and SBP at 12 months) [59,60], using generalized estimating equations and multivariable logistic regression models. This approach will allow us to present and interpret all outcomes in terms of absolute differences and a number-needed-to-treat [76].

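### Power to detect a 15-point difference in proportions with 60 per arm is about 37% for the plan's own example, not more than 80%

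*Protocol article*

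**What the plan says.** The section on sample size and power bases the trial on "a minimum total sample size of 120, with 60 in each arm", chosen for a 5-point mean difference on the PHQ-9, "assuming a repeated measures correlation of 0.6, and 2-tailed alpha of 0.05". It then says that the same sample provides "more than 80% power (two sided alpha = 0.05) to detect any between-group absolute difference in proportions of 15% or more", with the example "45% of usual care patients achieve depression remission vs 60% of intervention patients". On enrolment it says: "Anticipating a 40% attrition rate, we planned to recruit 168 patients in total across our 4 PCN sites".

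The Data analysis section plans between-arm comparisons of two kinds of proportion. One is remission, meaning a PHQ-9 score below 10 over three consecutive months. The other is clinically important change, defined as "achieving a reduction of 5 points on the PHQ-9 [44] or a 10% or greater improvement over baseline values for A1C, LDL cholesterol and SBP".

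The abstract puts the power claim more broadly: "Our planned enrolment of 168 patients will provide greater than 80% power to observe clinically important improvements in all measured outcomes".

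**The concern.** Everything needed to check the sentence on proportions is printed: the number per arm, the significance level, the sidedness, both rates and the claimed power. Rates near 50% are where a difference in proportions is hardest to detect, and 60 per arm looks far too few for a 15-point difference there.

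The remission and responder comparisons are to be turned into absolute differences and numbers needed to treat, for an audience of funders and care networks. If readers are told that power exceeds 80%, a non-significant remission result invites the conclusion that there is no worthwhile benefit. If true power is well under one half, that conclusion is not available.

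**Working it through.** **Inputs, all from the sample size section.** n = 60 per arm; two-sided alpha 0.05 (z = 1.960); p1 = 0.45; p2 = 0.60; claimed power above 80%. Planned enrolment is 168, or 84 per arm if split equally.

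**The plan's own figure.** Two-proportion normal formula, with pooled variance under the null and unpooled under the alternative:

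power = Φ[(|p2 − p1| − 1.960 × SE0) / SE1]

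- Mean rate = 0.525, so SE0 = √(2 × 0.525 × 0.475 / 60) = 0.0912.
- SE1 = √((0.45 × 0.55 + 0.60 × 0.40) / 60) = 0.0901.
- (0.15 − 1.960 × 0.0912) / 0.0901 = −0.318, and Φ(−0.318) = **0.375**.

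The stated figure is not reproduced.

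**Number needed for 80%.** n = [1.960 × √(2 × 0.525 × 0.475) + 0.842 × √(0.2475 + 0.24)]² / 0.15² = (1.384 + 0.588)² / 0.0225 = 172.8. That is 173 per arm, or 346 in total, about 2.9 times the 120 stated (186 per arm with continuity correction).

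**Other readings of the same example (45% vs 60%).**

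| Reading | 60 per arm | 84 per arm |
|---|---|---|
| Pooled normal, two-sided | 37.5% | 49.5% |
| Unpooled normal | 38.4% | 50.4% |
| Arcsine | 37.9% | 49.8% |
| Continuity-corrected | 30.7% | 43.3% |
| Exact enumeration, Pearson chi-square | 39.3% | 50.8% |
| One-sided 0.05 | 50.0% | 62.0% |
| Crediting a 0.6 correlation to the binary outcome | 45% to 54% | 59% to 68% |

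The last row is an assumption the plan does not make. It divides n by 0.80 (average of two measurements, or a change score), 0.73 (average of three) or 0.64 (covariance adjustment, 1 − 0.6²). If 120 or 168 were misread as the number per arm, power would be 64.5% or 78.9%. If 40% of the 168 were lost, 168 × 0.6 / 2 ≈ 50 per arm would remain, with power 32%.

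**Does it hold for any 15-point difference?** Power at 60 per arm, pooled normal:

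| Rates | Power |
|---|---|
| 0% vs 15% | 88.7% |
| 2% vs 17% | 80.8% |
| 3% vs 18% | 77.1% |
| 5% vs 20% | 70.5% |
| 10% vs 25% | 58.2% |
| 20% vs 35% | 45.2% |
| 30% vs 45% | 39.5% |
| 42.5% vs 57.5% (minimum) | 37.4% |
| 45% vs 60% | 37.5% |
| 70% vs 85% | 50.3% |

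By symmetry, 80% is reached again only when the higher rate is about 98% or more. The plan's example lies almost exactly at the minimum.

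**What is detectable.** For 45% vs 70% at 60 per arm, SE0 = 0.0903 and SE1 = 0.0873. Then (0.25 − 0.1769) / 0.0873 = 0.837 and Φ(0.837) = 0.799. So the detectable difference from 45% at 80% power is about 25 points. It is about 21 points at 84 per arm and about 27 points at 50 per arm.

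**Precision.** With 60 per arm and true rates of 45% and 60%, the 95% interval has half-width 1.960 × 0.0901 = 0.177. An observed 15-point difference would carry an interval of about −3 to +33 points.

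**The case against.** The strongest point on the other side is that no primary analysis is affected. The two primary outcomes are the PHQ-9 score and the scaled marginal model for continuous A1c, LDL cholesterol and systolic pressure. The 120 comes from the PHQ-9 mean difference, and the sentence on proportions is an addition to it. That is true, and nothing here shows that the mean-difference calculation fails. But the plan chose to state this power. It also allows the depression outcome to be treated as binary, and the abstract applies the claim to everything measured.

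A second point is that the intention-to-treat analysis with last observation carried forward could keep all 84 per arm. Power would then be about 49% (51% exact). So the statement that a true 15-point benefit would more likely than not be missed holds at the plan's 60 per arm. At 84 per arm it is close to even odds. Neither is near 80%.

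A third is that adjustment for baseline would help. The 0.6 correlation is stated for the PHQ-9 mean only, and every participant enters above the remission threshold, so remission has no informative binary baseline. Even the full credit leaves power at 68% or less.

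Finally, the article shows no power calculation for the second primary outcome. In a condensed article that is an omission at most, and the conclusion does not rest on it.

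**Conclusion.** The statement is wrong as printed. For the plan's own example at 60 per arm, power is about 37% (39% exact), less than half the figure claimed, and no standard method or reading of the sample size brings the planned enrolment to 80%. The extension to any 15-point difference is also false outside the extremes: for lower rates between 10% and 70%, power runs from about 37% to 58%. The abstract's claim is unsupported for the binary outcomes, since analysing all 168 patients gives only about 49%.

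The result assumes equal arms, independent patients and a simple comparison of two proportions, with the inputs as the plan prints them. It concerns the remission and responder comparisons only. The PHQ-9 mean-difference power could not be checked directly, because the article gives no standard deviation.

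**What to change.** 1. In the sample size section, replace the sentence on proportions with wording such as: *With 60 patients per arm and two-sided alpha 0.05, power is about 37% for remission of 45% versus 60%; 80% power is available for a difference of about 25 points (45% versus 70%).* Remove the claim that any difference of 15 points or more is covered.
2. In the abstract, confine the power claim to the PHQ-9 mean difference, the only other comparison for which the article states power. The sponsor should confirm that figure from its own calculation, including the standard deviation used.
3. Label remission, the 5-point PHQ-9 response and the 10% improvement outcomes as supportive, and report them as absolute differences with confidence intervals. A non-significant result should not be read as absence of benefit.

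The cost is wording only. The stated power becomes less favourable, but neither the recruitment target nor any primary analysis changes.

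### The 40% attrition allowance was added to 120 (giving 168) instead of divided out (giving 200), so the planned enrolment leaves about 101 completers against a stated minimum of 120.

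*Protocol article*

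**What the plan says.** The section on sample size and power considerations sets the base figure: "We estimate that a minimum total sample size of 120, with 60 in each arm, would provide power of 0.80". The target is "to detect a mean difference of 5 points in the PHQ-9", "assuming a repeated measures correlation of 0.6, and 2-tailed alpha of 0.05". No standard deviation is given.

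The same paragraph then moves from the base figure to the enrolment target: "Anticipating a 40% attrition rate, we planned to recruit 168 patients in total across our 4 PCN sites". It applies no other factor and expressly declines to inflate for clustering by physician.

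The abstract (Methods/design) attaches the power claim to the enrolled number: "Our planned enrolment of 168 patients will provide greater than 80% power to observe clinically important improvements in all measured outcomes".

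**The concern.** The paragraph prints three figures that should be linked by one step: a required number (120), a loss rate (40%) and an enrolment target (168). An allowance for attrition exists so that the required number is still there at the end. Here it is not, because the loss rate seems to have been applied to the 120 who must remain and not to the larger number from whom the losses occur.

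At stake is the power the trial can claim. A reader of the abstract would take a null result as coming from a study with more than 80% power. On the protocol's own inputs, the enrolment of 168 does not support that figure at the attrition it expects.

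**Working it through.** **Inputs**, all from the protocol article's sample size section:
- required total n = 120 (60 per arm, 1:1), said to give power 0.80
- attrition d = 0.40
- planned enrolment N = 168
- two-sided alpha 0.05, PHQ-9 difference 5 points

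**1. Reproduce the stated enrolment.**
- n × (1 + d) = 120 × 1.40 = 168. This matches exactly.
- n / (1 − d) = 120 / 0.60 = 200. This does not match.

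The protocol does not write out the multiplication, so the first form is inferred. It matches to the patient, and no other stated factor produces 168.

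**2. Completers under the plan's own attrition.**
- N × (1 − d) = 168 × 0.60 = 100.8, or 50.4 per arm.
- Shortfall: 120 − 100.8 = 19.2, and 19.2 / 120 = 16%.

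This step does not depend on how 168 was reached.

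**3. Attrition that 168 can absorb.**
- 1 − 120/168 = 48/168 = 28.6%.

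**4. PHQ-9 power at the reduced number.** Take the protocol's 0.80 at 60 per arm as given. The expected test statistic is then 1.960 + 0.842 = 2.802, and it scales with the square root of the number per arm:
- 50.4 per arm: Φ(2.802 × √(50.4/60) − 1.960) = Φ(0.608) = 0.728
- 50 per arm: Φ(2.802 × √(50/60) − 1.960) = Φ(0.598) = 0.725

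The standard deviation and the correlation of 0.6 cancel in the ratio, so neither is needed.

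**5. What the missing standard deviation hides.** For 5 points at 60 per arm to give exactly 80% power, the effective standard deviation must be 5 / (2.802 × √(2/60)) = 9.8 points. Under baseline adjustment with correlation 0.6 (variance factor 1 − 0.36 = 0.64), that corresponds to a raw value of 12.2. Under change scores (factor 2 × (1 − 0.6) = 0.80), it corresponds to 10.9. With assumed values and no baseline adjustment, power is:

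| Assumed SD | 60 per arm | 50.4 per arm |
|---|---|---|
| 8 | 0.928 | 0.881 |
| 9 | 0.861 | 0.796 |
| 10 | 0.782 | 0.709 |

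**6. The proportions example (45% vs 60%).** The normal approximation with pooled variance under the null gives 0.375 at 60 per arm and 0.322 at 50 per arm. Most of this deficit is there before any attrition: all 168 patients (84 per arm) would give only 0.495. Attrition takes about 0.05 off a figure that is already far below the claimed 80%, so the low power for proportions is mainly a separate error.

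**The case against.** Three points can be made for the plan.

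**The 73% depends on an unverifiable base.** This is true. With no standard deviation stated, 120 cannot be re-derived. If the real standard deviation is smaller than the calculation implies, PHQ-9 power may exceed 80% even with about 50 per arm (0.881 at an assumed value of 8). The 73% must therefore be presented as conditional on 0.80 at 60 per arm. The gap between 101 and 120 does not share this weakness, since it uses only printed figures.

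**The analysis keeps all 168.** The data analysis section plans intention-to-treat with last observation carried forward, and some patients lost before month 12 will have 6-month data. So 50 per arm is a simplification of the analysed number. But carrying values forward does not restore the lost 12-month information, and the sample size section does not rely on it; if it made attrition harmless, no allowance would be needed. Take the extreme case in which 40% of each arm has its baseline carried forward. A 5-point difference in change shrinks to 5 × 0.6 = 3 points, and the variance of change falls at most to 0.6 of its value. The standardised signal at 84 per arm is then at best proportional to 3 × √(84/0.6) = 35.5, the same as 5 × √50.4 = 35.5 for completers alone. Later dropout would soften this.

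**The consequence is limited.** Design, estimand and analysis do not change, and only the abstract's power statement is attached to 168; those in the sample size section are attached to 120. That narrows the correction, but the enrolment target and the abstract's claim remain wrong as written.

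**Conclusion.** The concern holds. The protocol's minimum of 120, attrition of 40% and enrolment of 168 cannot all stand: at 40% attrition, 168 leaves about 101 patients, and 120 would need 200 enrolled (32 more). This rests on printed figures alone.

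The fall in PHQ-9 power from 80% to about 73% rests on two assumptions: that 60 per arm gives exactly 80%, and that information at 12 months comes from the completers. The abstract's claim of more than 80% power does not follow from the plan's inputs unless attrition stays below 28.6%. The correction is needed because the trial relies on this sample size and power statement.

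**What to change.** Keep the enrolment of 168 and correct the statements around it.

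1. In the sample size section, replace the attrition sentence with wording such as: *With 40% attrition, 168 enrolled patients yield about 101 with 12-month data (about 50 per arm). If 60 per arm gives 80% power for a 5-point PHQ-9 difference, this number gives about 73%. Enrolling 168 leaves 120 only if attrition is 28.6% or less.*
2. State the PHQ-9 standard deviation and how the correlation of 0.6 enters, then recompute the detectable PHQ-9 difference at 50 per arm. If that calculation gives a different power, it should replace the conditional 73%.
3. Correct the abstract's power claim to match, naming the outcome and the attrition it assumes.

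The cost is wording only, with a somewhat less favourable power statement. No extra enrolment is required. A sponsor who wants to retain 120 patients at 40% attrition would have to plan for 200.

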### Broader RE-AIM evaluation

#### Reach

Using demographic information and eligibility criteria, a comparison of patient characteristics between the intervention and usual care groups will be conducted to address reach. Aggregate demographic information between participants and non-participants will be compared using population-level data available through the Alberta Diabetes Surveillance System [77]. Information on reach will also be documented through a patient recruitment tracking system, the PCNs’ diabetes patient registries, and monthly reports on recruitment submitted by PCN staff.

#### Implementation, including cost-effectiveness

Implementation evaluation is used to examine the extent to which an intervention is delivered as planned, particularly in real world practice settings. This type of evaluation explores why an intervention is successful or not, and can contribute to the successful realization of programs in the future. Implementation evaluation of TeamCare-PCN will enhance our contextual understanding and interpretation of why the intervention had an impact or not, in which settings (i.e. PCNs), and for whom. It also provides a mechanism for continuous quality improvement by generating ongoing information. Implementation evaluation is also crucial to determine the sustainability of a program, as it is used to inform future decision-making and strategic planning by identifying critical successful factors for implementation (such as resources, staff qualities, and leadership) and recommendations to mitigate barriers.

We will examine the intended versus actual implementation of TeamCare-PCN through several means: document review; pre/post training survey of CMs to assess knowledge and confidence with the model; usual care checklist documenting organizational priorities and systems to implement the model; baseline, mid- and post-intervention interviews with PCN staff regarding facilitators and barriers to implementation and recommendations for improvement; and participant-observation.

A number of economic evaluations of team-based interventions in patients with diabetes and depression have been conducted [30,78-80]. Incremental cost-utility ratios have been estimated at less than $400 per quality-adjusted life year gained [78]. While the consistent economic benefit of these interventions has been demonstrated, these evaluations are highly dependent on many factors including the implementation strategies of these interventions in the primary care settings of the single urban managed care environment in the US. We will therefore conduct an economic evaluation of the TeamCare-PCN implementation, using a similar methodological approach. To do this, we will use primary data collected during the study period, health care utilization data obtained through linkages with administrative databases, as well as an Alberta-based economic model to estimate future diabetes related costs [81]. For our economic evaluation models, we will take the perspective of the individual PCN Board as the main decision maker, with a second perspective of the third-party payer, that is, the provincial health care system, along with our analyses focusing on direct medical costs, as this is the most relevant perspective for our decision-making partners.

##### Intervention costs versus usual care costs

Costs for the intervention will be estimated using the actual salary and benefits for the Care Manager and Administrative Assistant provided for the intervention plus a 30% overhead rate for PCN space and management costs [82]. The CM time will be estimated based on the actual visits with intervention patients, for both in-person and telephone contacts, as well as outreach efforts and record-keeping. Intervention costs will also include a fixed amount for each participant assigned to the intervention program to defray the costs of specialist supervision and the clinical management support.

##### Health care utilization data

Patients enrolled in the study will be asked for permission to access their medical records by providing their personal health number, thus allowing linkage to provincial health care administrative data from Alberta Health and Wellness (AHW) for physician, hospital, and emergency department billing, and pharmaceutical data (for patients 65 years and older). This linkage will allow health care utilization and health care costs to be included in the evaluation. These data sources are regularly monitored as part of the Alberta Diabetes Surveillance System (ADSS) [77].

